### Recruitment and retention plan

For phase 1, focus groups will be completed prior to the beginning of phase 2. Recruitment will utilize participants from the community-based participatory research study (NCT01927783) for the focus groups, as well as adults associated with collaboration sites of the DC CHOC. Initial contact will occur through phone contact with identified eligible participants. Likewise, email announcements will be sent to collaboration sites. Recruitment of focus group participants will use a purposive snowballing sample of African-American adults (age > 18) who live in wards 7 or 8 in Washington D.C. However, we will aim for the study recruitment to lead to variation in demographic subgroups. Identified participants may or may not be currently enrolled in or participated previously in a community cooking education program/class. At the time of phone contact with potential participants, study staff will ask screening eligibility questions regarding self-reported risk for cardiovascular disease. If potential participants are deemed eligible based on aforementioned inclusion/exclusion criteria, they will be invited to participate in a focus group.

For phase 2, similar strategies for identifying participants will be used as in phase 1. At the time of contact with potential participants, study staff will ask screening eligibility questions regarding self-reported risk for cardiovascular disease. If potential participants are deemed eligible based on aforementioned inclusion/exclusion criteria, they will be invited to schedule a baseline visit. Signing of informed consent document for the protocol will be obtained at clinical visit #1 (TP_0_) after discussion and explanation of study requirements with a member of the research study team. Eligible study participants will have consent document mailed to them to review prior to clinical visit #1*.* The planned flow and steps of data collection within phase 2 relevant to expected recruitment and retention are illustrated in Fig. 4.

**Fig. 4 Fig4:**
[figure not shown]
The planned flow and steps of data collection within phase 2 relevant to expected recruitment and retention

Retention efforts focused on participant engagement include reminder phone calls to participants on a weekly basis during the intervention and 1 week and 1 day prior to all clinical visit appointments. Participants will be discontinued from the study if any of the following should occur: participant requests to be removed from the study, participant does not participate in the initial clinical visit, or participant is unable to participate in the intervention component.

## Analysis

### Qualitative data

A phenomenological methodological approach will be undertaken in both phase 1 and 2 to understand participants’ lived experiences with cooking at home within the context of their neighborhood and household. Phase 1 will focus on gathering an understanding of non-intervention based conditions. While in phase 2, we will gather an understanding of the participation experience within the specific setting of the cooking intervention. In both phases, qualitative data collection and analysis will use the four criteria that comprise the rigorous standards for qualitative research: credibility, dependability, confirmability, and transferability [69]. Credibility will be maintained by the independent analyses of our transcribed interview data to ensure that our theme categories cover all relevant data. Credibility will be further strengthened through the consensus-building process, which will ensure that similarities within and differences in our theme categories are thoroughly evaluated. Dependability will be established by maintaining facilitator consistency through data collection and through data analysis by our team. Confirmability will be supported by developing an electronic, thematic database and through the preservation of interviewer perceptions via interview/focus group field notes. Our diverse study team, comprising individuals with various clinical and research-related expertise with members of the community, will support the criteria of transferability.

In phase 1, the sources for qualitative data are the transcripts and research team field notes from the focus groups. In phase 2, the source of the qualitative data will come from semi-structured interviews conducted at all study time points. Analysis in both phases will use the de-identified verbatim transcription of audiotapes and field notes written by research team members. Members of the research team will develop a codebook based on themes from the interviews. Each thematic code will be accompanied by an operational definition that will allow for clarity and consistency in the coding process. A team of coders will independently review all transcripts. Discordant coding will be discussed until consensus among the coding team is achieved. Once the iterative process of consensus building is complete, an intramural expert in qualitative methodology will validate the final themes and coding. After data are coded, NVivo will be utilized for data management.

### Quantitative data

#### Sample size justification

For phase 2, sample size justification was done in accordance with Billingham et al. [70]. From the literature for published cooking interventions, intervention group size ranges from 12 to 30 participants [13–15, 43]. We therefore selected a sample size of 30 participants for phase 2. We also based the sample size on expected attrition. From our previous community study (NCT 0192778 [34];), we anticipate a 33% attrition rate for the first clinical visit. Therefore, in order to reach 30 participants, we plan to screen 45 participants*.*

#### Data analysis

Baseline demographic and clinical data will be analyzed using descriptive statistics. Categorical data will be presented as frequencies and percentages, while continuous data will be presented as means and standard deviations. Patterns of missing data will be examined thoroughly to assess whether any questions were systematically skipped by all participants or any sub-group of participants.

All continuous variables of interest for quantitative data analysis will have baseline evaluation done to check for outliers and normal distribution. Data determined to not have normal distribution will be expressed as medians with interquartile ranges. If the assumptions of normality are not violated, we will proceed with parametric testing. If the assumptions of normality are violated, non-parametric tests will be utilized. For quantitative analyses, statistical significance will be considered at two-tailed, *p* < 0.05. Statistical analysis will be conducted in available statistical software (for example SAS, SPSS). Inferential statistics will be conducted for the purposes of exploration, but without placement of conclusions on the effectiveness of the intervention. Relationships between variables will be examined with bivariate correlation coefficients (for two continuous variables), Chi-squares (for two categorical variables), and *t* tests. Analysis of variance (ANOVA) (for one categorical and one continuous variable) will be conducted to explore sub-group analysis. Linear or logistic regression analyses, with multivariate analysis when applicable, will also be pursued to examine determinant models of cooking behaviors or feasibility measures.

Phase 2 consists of four time points. Group level analyses will be conducted with reporting and comparison of group means at each time point. Within-person analysis using repeated measures will also be done to compare within person changes across time points, including repeated measures ANOVA and *t* tests where applicable.

For the survey responses related to the primary outcomes, facilitators, and barriers to cooking (DC CHOC, CAFPS, CES), question items deemed as positively related to facilitating cooking will have a sum of scores calculated and then divided by total number of respondents. Survey items deemed as negatively related to cooking (barriers) will be reverse scored to determine mean scores. Within DC CHOC Survey, responses for cooking perception will be dichotomized as agreement with cooking if response is ≥ 5, as reported in Wolfson 2016 [71].

From the cooking diaries, daily cooking frequency amounts will be aggregated into cooking frequency for each week of the study, the average at each time point of phase 2 for each participant. Cooking frequency at each time point will also be dichotomized based on the average cooking frequency per week of 10.8 out of 21 possible meals, as reported in a national survey of U.S. adults [71].

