## Study outcome measures

### Primary outcomes

The primary outcomes for this study are feasibility measures, home cooking behavior, and objective evaluation of cooking motor and process skills. In order to determine feasibility of the cooking intervention, we are collecting information on number of screened participants, number of participants enrolled, attendance at intervention sessions, and attrition rates. Attendance will be taken at each session. At a minimum, participants are counted as an attendee when one full intervention session has been completed. Completers of the intervention will be defined as participants who complete all six intervention sessions. Dropouts for the study will be defined as those who attend the first clinical visit, but do not attend any intervention session by the date of the final session. Attrition rates will be determined from the number of participants who stopped participating divided by the average number of participants at each time point, and over the total study period (see Fig. 4 for time points). We anticipate that our attrition rates will be at or below 33%, which is the reported attrition rate for this target population based on members of the research team’s experience recruiting from wards 7 and 8 [34]. Feasibility success will be achieved if the majority of participants (> 50%) reach 50% participation (3/6 sessions). This is based on two reports in the literature of cooking intervention studies among African-Americans in which this attendance metric was met [13, 15]. Information collected on feasibility and cooking behavior and skills will allow for appropriate sample size calculations for future studies.

Cooking behavior will be determined through multiple variables to provide a convergence of data. Using paper cooking diaries, participants will be instructed to start daily recording of home cooking following the initial clinical visit and will stop after the last visit, for a total collection time of 18 weeks. The design for the cooking diaries is fixed-schedule (once per day). Each daily entry will consist of marking the frequency of cooking at home, as well as commenting on enjoyment, interest [47], and perception of cooking skills.

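### Repeated measures ANOVA and visit-by-visit group means can show change that is due to selective loss; a mixed model on all available visits and diary rates per recorded day would be safer

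*Protocol article*

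**What the plan says.** All references are to the protocol article.

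- **Within-person contrast (Data analysis).** "Within-person analysis using repeated measures will also be done to compare within person changes across time points, including repeated measures ANOVA"; t tests are added where applicable.
- **Group contrast (Data analysis).** "Group level analyses will be conducted with reporting and comparison of group means at each time point". No group is assigned in this study, so I read this as the cohort mean at each visit. No common set of participants is named.
- **Diaries (Data analysis).** "daily cooking frequency amounts will be aggregated into cooking frequency for each week of the study", then averaged per participant at each time point and dichotomised at an "average cooking frequency per week of 10.8 out of 21 possible meals".
- **Loss (Primary outcomes).** "We anticipate that our attrition rates will be at or below 33" per cent. The rate is the "number of participants who stopped participating divided by the average number of participants at each time point", and is also taken over the whole study. Dropouts are people who attend the first clinical visit but no session.
- **Discontinuation (Recruitment and retention plan).** A participant unable to take part in the intervention component is discontinued.
- **Loss (Sample size justification).** "we anticipate a 33% attrition rate for the first clinical visit", and therefore "in order to reach 30 participants, we plan to screen 45 participants".
- **Timing (Table 2, Primary outcomes).** Clinical visit measures fall at TP0, TP2 and TP3; AMPS at TP0 and TP2 only. TP1 is the intervention.

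**The concern.** By the article's own definitions, non-engagers can be present at TP0 and absent at TP2 and TP3. They are unlikely to be a random subset. A TP3 mean then describes a different set of people from the TP0 mean, and an ANOVA restricted to people with every visit estimates change in a selected group.

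A similar problem affects the diaries. A cut on a 21-meal week presumes seven recorded days, and the article does not say whether the weekly figure is a sum or a rate per recorded day. If it is a sum, a blank day counts as a day without cooking.

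Home cooking behaviour is a primary outcome, and the Primary outcomes section says these data will support sample sizes for future studies. A distorted change estimate would carry into that planning.

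**Working it through.** **1. The plan's own figure.** 30/(1 − 0.33) = 44.8, rounded up to 45. The number to screen reproduces, but only with the 33% lost between screening and the first clinical visit. The Primary outcomes section applies the same 33%, as an upper limit, to each time point and the whole study.

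**2. If 33% were also lost after enrolment.** A simple rate leaves 30 × 0.67 = 20.1, about 20 people. With the article's average-number denominator, the number lost L solves L/(30 − L/2) = 0.33, so L = 9.9/1.165 = 8.5, leaving 21.5.

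**3. Group means with no individual change.** Let a fraction f leave, and let leavers cook d meals/week less than stayers. The mean of everyone is (1 − f) × stayer mean + f × leaver mean. The mean of those who remain is the stayer mean. The shift is f × d.

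| Loss f | d = 1 | d = 2 | d = 3 | d = 4 |
|---|---|---|---|---|
| 0.33 | 0.33 | 0.66 | 0.99 | 1.32 |
| 0.15 | 0.15 | 0.30 | 0.45 | 0.60 |

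The gap d and the 15% loss are assumptions.

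**4. Both contrasts, true mean change 0.** Simulation with assumed values: n = 30, between-person SD 4, visit SD 3, slope SD 2 per visit in the last row, about 34% lost, 4000 runs. Results are in meals/week.

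| Loss depends on | TP3 observed minus TP0 all | Change in completers |
|---|---|---|
| nothing (random) | 0.00 | −0.01 |
| stable cooking level | +1.46 | −0.01 |
| observed baseline value | +1.19 | −0.64 |
| own trajectory | +1.51 | +1.50 |

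**5. The alternative, true mean change +1.0.** Simulation with assumed SD 4, correlations 0.5 to 0.6 and about 20 of 30 retained. The ranges cover two versions of the loss model.

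| Loss depends on | Complete-case | Group means | Likelihood-based |
|---|---|---|---|
| TP2 value | 0.99 | 1.67 to 1.86 | 0.98 to 0.99 |
| TP2 − TP0 change | 1.57 to 1.76 | 1.11 to 1.16 | 0.99 to 1.01 |
| baseline | 0.30 to 0.43 | 1.57 to 1.73 | 1.00 to 1.02 |

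The last column is close to 1.0 partly by construction, because loss depends on observed values in every row.

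**6. Diaries, if the weekly figure is a sum.** A person cooking 1.7 meals/day scores 1.7 × 7 = 11.9 in a full week and 1.7 × 6 = 10.2 with one blank day. The classified value, however, is the time-point average. Over the six weeks of TP1 the full total is 1.7 × 42 = 71.4, and the cut corresponds to 10.8 × 6 = 64.8. Three blank days give 66.3/6 = 11.05, above the cut. Four give 64.6/6 = 10.77, below it. A steady 12 meals/week recorded on 80% of days would sum to 9.6. With 7 × meals per recorded day, the first person stays at 11.9 and the second at 12, provided blank days are unrelated to cooking.

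**The case against.** The case against is substantial, and much of it stands.

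- **The methods list is open.** t tests are named too, and a paired test needs only two visits. The within-person analysis directly follows the group means. Dropping people with a missed visit is a property of classical ANOVA, not something the article states.
- **The article does not plan raw diary totals.** A reader might infer them, but the aggregation wording does not settle sum or rate. Detailed rules for lost visits and blank days may sit in a plan that is not shown, and their absence is no finding.
- **Bias is not certain.** A reader might infer that loss will be reported as behaviour change. Random loss produces none, and change in completers is unaffected when loss follows only a stable cooking level. Selective loss and blank days can also push in opposite directions.
- **One-third lost in follow-up is not established.** It is an upper limit in one section and belongs to the first clinical visit in another.
- **The 10.8 cut is easily over-read.** The article compares no group mean with it, and one blank day does not reclassify the example person over TP1; four of 42 are needed.
- **There are safeguards.** Attrition is reported by time point, missing or unusable data count towards participant burden, and a 7-day survey measure of cooking frequency runs alongside the diary.
- **Inference is declared exploratory**, with no conclusion on effectiveness. The attendance criterion for feasibility is untouched.

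What remains is that the article names these contrasts, foresees selective loss after baseline, and could use a better method on the same data.

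**Conclusion.** The point holds in a limited form. The named contrasts can move without individual change if loss is related to cooking level or early change. For group means the size is f × d: about 0.33 meals/week per 1 meal/week gap at one-third loss, and 0.15 at 15% loss. For completers, the simulated error ran from −0.64 to +1.50 meals/week with a true change of zero, depending on the mechanism. Gaps, SDs, correlations and loss mechanisms are assumptions; only the 33%, the sample of 30 and the 10.8 cut come from the article. The consequence is distorted description and weaker planning figures for later studies, not a false claim of efficacy. For diaries, the defect is an undefined weekly figure set against a seven-day cut.

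**What to change.** - **Outcomes at TP0, TP2 and TP3.** Replace repeated measures ANOVA with a linear mixed model (REML, categorical time, small-sample degrees of freedom) on all available visits from everyone with TP0. Report change with 95% CI, and show change in the same participants beside the visit means.
- **AMPS.** Use the TP0 to TP2 change.
- **Diaries.** Define weekly frequency as 7 x meals per recorded day before averaging and applying the 10.8 of 21 cut. Report recorded days per week. A minimum such as 4 of 7 days, or a Poisson or binomial model with recorded days as offset or denominator, is optional.
- **Attrition.** Reconcile the 33% in Primary outcomes with the 33% in Sample size justification, and state which stage each covers.

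The cost is a change of wording and slightly more programming; no new data are needed. The model corrects only for loss explained by observed data. It does not repair loss driven by a trajectory that was never seen, and the per-day rate assumes that blank days are not themselves days without cooking.

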## Data collection and management

All analyzed data will have unique, study-specific numerical identifiers so that research data can be attributed to an individual human subject participant. Data obtained during the conduct of the protocol will be kept in secure password-protected network drives or in approved alternative sites that comply with NIH security standards. This includes recorded participant interviews. The principal investigator and associate investigators, research nurses, and/or contracted data managers will assist with the data management efforts.

Survey measures will be collected electronically on clinic tablets used by participants on clinical visit days. Laboratory data and clinical examination data will be collected using the Clinical Center electronic health record known as Clinical Research Information System (CRIS). Cooking diary data will be completed by paper format and then entered electronically and managed using REDCap electronic data capture tools hosted within the Biomedical Translational Research Information System (BTRIS) at the NIH. REDCap (Research Electronic Data Capture) is a secure, web-based application designed to support data capture for research studies [72]. REDCap was developed and is licensed by Vanderbilt University. All use of REDCap will occur in compliance with NIH security standard. Participants without a personal electronic device will have paper cooking diaries provided for mail return to the research team in pre-stamped, self-addressed envelopes. The diaries will then be entered using a double-data entry method into a secure data management system.

Data from enrolled subjects will be stored until they are no longer deemed of scientific value or if a subject withdraws consent for their continued use, at which time they will be destroyed. Should we become aware that a major breach in our plan for tracking and storage of data has occurred, the Internal Review Board (IRB) will be notified. Each NIH protocol undergoes a yearly departmental, independent audit in addition to yearly continuing reviews by the IRB.

Data management committees (DMC) are not usually warranted in early studies such as pilot/feasibility studies, but formal monitoring groups may be useful for certain types of early clinical studies [73]. For this protocol, a study monitoring group consisting of study investigators will be formed and meet regularly throughout the study time frame. Safety monitoring will occur following standard procedures within the NIH. These procedures include reporting of adverse events related to participation in the study. Adverse events will be reported to the principal investigator (PI) with recommendations and follow up, as well as documentation in the clinical electronic patient record. Adverse events will focus on ones related to the intervention and clinical visits where the NIH is involved either directly or indirectly by recommending certain interventions. Adverse events associated with the cooking intervention will be monitored by the PI, serving as safety officer, and will be reported to the IRB as appropriate and as part of the annual report.

### Evaluation of risks/discomforts and benefits ratio

This protocol will assess feasibility of administering a cooking behavior intervention in a community at risk for CVD within a food desert. Participation in phase 2 may confer a health-behavior, nutrition education based benefit to participants. However, it is possible that there may be no direct benefit. It is also possible that in both phase 1 and phase 2, answering survey questions may cause discomfort to participants. Furthermore, in phase 2 phlebotomy for laboratory study collection may lead to discomfort at the puncture site. If this should occur, every effort will be made to address and minimize participant discomfort.

### Compensation

Participants will be compensated for research-related discomfort and inconveniences in accordance with NIH guidelines. If participants are unable to finish the study, they will be paid only for those parts completed.

### Dissemination of results

This protocol was developed in collaboration with the DC CHOC community advisory board. Therefore, results of the study germane to the primary and secondary outcomes as well as results determined to be related to stated dietary behavior concerns voiced by the committee, will be presented at the DC CHOC committee meetings. Publications related to baseline data and primary outcomes will be disseminated to study participants once published.

Since the protocol is federally funded, any manuscript to be published in a peer-reviewed journal will be submitted to PubMed Central or public access upon acceptance for publication.

